### **Logistical and ethical considerations**

Clearance will be sought from the Graduate School, Kenyatta University and a research permit obtained from the Ministry of Education. Authority to conduct research will be obtained from the Ministry of Health, Thika and the local chief. Ethical approval will be obtained from the KEMRI National Ethical Review Committee and a thumb print or written informed consent sought from the parents, after explaining the purpose of the study without revealing the study hypotheses. The food supplements will also be given to all the underfive children in the intervention households. Sick children will be advised to seek further medical attention at Thika Level 5 Hospital. Blood will be drawn two times during the study from children whose parents consent. The information provided will be treated in the strictest confidence and none of the participants will be individually identifiable in the resulting thesis and that it will be used for the purpose of the study only. The outcome of research will be communicated to the respondents.

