### **Intervention phase**

### **Target population**

The study will target Moderately Malnourished (MM) children 6-36 months old with height weight for height (WH) within -3 and less than -2 Z-scores or with/and a mid-upper arm circumference (MUAC) within the range of 115-125 mm without bilateral oedema. The age 6-36 months is a period of rapid growth, highest nutrient requirements and poor diets predispose children to a risk of zinc deficiency. The beneficial effect of zinc may be limited to children with pre-existing growth failure (IZiNCG, 2004b) hence the study targets MM children. The respondents will be the mothers/primary caregivers to the children.

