### **Inclusion criteria**

MM children (6-36) months, whose parents consent, willing to be visited in their homes and intending to stay in the area during the study period and who will have stayed in the area for the past 6 months will be recruited.

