### **Description of the intervention**

CSB (80% corn and 20% soy) and sprinkles meeting 100% RDA of zinc will be sourced from suppliers. For a period of six months, sprinkles (1g) will be added to corn-soy porridge once daily and CSB porridges made from 100g flour will be given daily (Figure 1). The micronutrient composition of the different study groups is shown in Table 1. The food supplements will be prepared in feeding centres. De-worming will be done at the start of the intervention using mebendazole (500 mg). Demonstrations on porridge preparation and use of sprinkle and nutrition education focused on the importance of nutritious diet will be given to the primary caregivers on group basis at baseline.

Table 1: Micronutrient composition of sprinkles and CSB

|                  | Expt Gp 1:
Sprinkles (per 1
g sachet) | Expt Gp 2:
Sprinkles* (per 1
g sachet) | Expt Gp 3:
Sprinkles* (per 1
g sachet) | Comparator Gp
4: CSB ( 100g
dry wt.) |
|------------------|------------------------------------------------------|-------------------------------------------------------|-------------------------------------------------------|-----------------------------------------------------|
| Vit A (IU)       | -                                                    | 1250                                                  | 1250                                                  | 1300                                                |
| Vit E (mg)       | -                                                    | 6.0                                                   | 6.0                                                   | -                                                   |
| Vit C (mg)       | -                                                    | 30                                                    | 30                                                    | 30                                                  |
| Thiamine (mg)    | -                                                    | 0.5                                                   | 0.5                                                   | 0.1                                                 |
| Riboflavin (mg)  | -                                                    | 0.5                                                   | 0.5                                                   | 0.4                                                 |

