### 3.4.6 Sample size determination

Determination of sample size will be based on the primary objective and the formula by Liu

& Chow (1992). Where; 
$$n = \frac{(Z_{\alpha} + Z_{\beta})^2 \sigma^2}{(\delta - \varepsilon)^2} = \frac{(1.64 + 1.28)^2 0.71^2}{(0.2 - 1.0)^2} = 67$$

Where; n = No. of study subjects per group,  $\sigma$  = variance within the groups,  $\delta$  = expected outcome difference of the groups (20 % as per the bioequivalence rule),  $\varepsilon$  = the absolute values of proportion differences among the groups. The standard normal deviate at the required confidence interval (95 probability error).

The prevalence of zinc deficiency in Kenya is 50% (GOK & UNICEF, 2008). The estimated post-intervention prevalence of 20%, 10%, 20% and 50% for the reference, ZN, ZN in MMN and MMN without ZN groups respectively. To show equivalence within 20% rule with 80% power and 5% significance, a sample size of 67 per group was obtained and allowing 20% attrition, a sample size of 80 per group is obtained.

Where; n = The desired sample size, z = The standard normal deviate at the required confidence interval (95 probability error equal to 1.96), p = The proportion of occurrence of the phenomenon (0.5) since prevalence is 50%, q = The proportion of non-occurrence is (1-P) = 0.5, d = level of statistical significance (0.05 for 95% level of significance).

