### **Recruitment of study participants**

Door-to-door visits will be done to identify families with the target children. The children will then be screened by a clinical officer. The consent form and procedures of the intervention will be explained to the parents of the eligible children and a thumb print or written informed consent obtained from the interested parents. A follow up will be done within 2 days to start the intervention.

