### **Anthropometric measurements**

Weight will be measured on a pediatric balance-beam scale to the nearest 0.1 kg while length/height to the nearest 0.1 cm taken when nude. Recumbent length will be taken for children less than two years or those whose length is shorter than 87cm and height for those whose length is greater than 87 cm. Age as per birth date (Child Health Cards) will be taken. When such evidence misses, age will be estimated using the parent's estimates or local event calendars. Oedema will be confirmed if a shallow print remains on both feet, after applying thumb pressure for 30 seconds to the two feet simultaneously. ENA for SMART software will be used to standardize anthropometric measurements.

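### The household supply rule covers all under-fives with no lower age limit, so as written it reaches siblings under 6 months, for whom the protocol offers no rationale, amount or screening

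*Protocol*

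**What the plan says.** Protocol, *Logistical and ethical considerations*, extends the supplement beyond the enrolled child: "The food supplements will also be given to all the underfive children in the intervention households". The sentence gives no amount, no lower age and no condition. The one after it is a general referral: "Sick children will be advised to seek further medical attention at Thika Level 5 Hospital".

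The supplement is defined in *Description of the intervention*: "For a period of six months, sprinkles (1g) will be added to corn-soy porridge once daily", or, in the comparator group, a daily CSB porridge made from 100 g of flour. Table 1 gives one composition per study group and has no age columns.

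Enrolment is limited by age. *Inclusion criteria* begins: "MM children (6-36) months, whose parents consent, willing to be visited in their homes". *Target population* gives the reason: "The age 6-36 months is a period of rapid growth, highest nutrient requirements".

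**The concern.** Feeding the other young children in a household is sensible, and it may keep the enrolled child's ration from being shared out. The difficulty is the reach of the rule. Under five years, with nothing further, includes newborns. The supplement is a porridge carrying micronutrients, and the protocol has considered its use only from 6 months upward. Anyone who follows the text at a feeding centre is told to supply every under-five in the household and has no written ground for leaving out a young infant.

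What is at stake is the protection of non-enrolled siblings. No trial result depends on it.

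**Working it through.** The plan has no figure to reproduce. The check sets the age limits side by side and looks for any text that narrows the supply rule.

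**Age limits as written**
- Household supply (*Logistical and ethical considerations*): under five years, that is 0-59 months.
- Target population and its rationale (*Target population*): 6-36 months.
- Enrolment (*Inclusion criteria*): 6-36 months.

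The supply rule therefore extends past the rationale at both ends: 0-5 months below it and 37-59 months above it.

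**Does any other section narrow the rule for siblings?**
- *Exclusion criteria* applies to children being recruited.
- *Recruitment of study participants* has a clinical officer screen the target children. No such step is described for siblings.
- *Description of the intervention* fixes one daily portion and does not grade it by age. It says that the sprinkles meet 100% of the zinc RDA without naming the age band.
- *Data analyses* cites infant-feeding guidelines only as indicators for assessing feeding practices.

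No section supplies a lower age.

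**How long an infant could fall under the rule.** The intervention lasts six months. Time below 6 months of age, counted from the start, is 6 minus the age at start in months:
- newborn at start: 6 − 0 = 6 months, the whole intervention;
- exactly 5 months old at start: 6 − 5 = 1 month;
- just short of 6 months at start: a few days.

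This is time covered by the wording. It is not intake, because no amount for siblings is stated.

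**How many infants.** *Sample size determination* plans 80 children per group ("allowing 20% attrition, a sample size of 80 per group is obtained"), so 4 × 80 = 320 enrolled children. That means at most 320 households, reached if each holds one enrolled child. If intervention households means only the three sprinkles groups, the ceiling is 3 × 80 = 240. The documents say nothing about the share of these households with an infant under 6 months, so the count cannot be derived.

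**The case against.** The strongest reply is that 6 months is an enrolment limit. *Target population* explains whom to study and does not say that the supplement is unsuitable for anyone else, so the supply sentence contradicts nothing. By the same reasoning, siblings aged 37-59 months also lack a rationale, yet the correction would keep them. The authors may simply have meant under-fives who already eat porridge. The team demonstrates porridge preparation, gives nutrition education, asks about complementary foods and monitors feeding practices, so it is unlikely to be careless about infant feeding.

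Much of this stands. A reader might infer a breach of the eligibility criteria, but those criteria govern enrolment and siblings are not enrolled. A reader might also infer that young infants would receive a 1 g sachet or a 100 g porridge portion daily. The sentence states no amount for siblings, so no dose can be claimed.

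The reply does not remove the point. The supply sentence is an instruction, and the restriction to children already eating porridge appears nowhere in it. The two ends of the age range also differ in the text: the authors chose five years as the upper limit, whereas no lower limit was chosen. The only starting age that the protocol itself uses is 6 months.

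**Conclusion.** The point holds as a minor safety correction for non-enrolled siblings. It rests on the ordinary meaning of the sentence and on the absence of a lower age limit anywhere else in the protocol; both can be checked in the text. Its size is the first 6 months of life, with between a few days and the full six months of the intervention falling under the rule for an infant already in the household at the start.

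Two stronger readings should be resisted. One is that infants are shown to be harmed or exposed: the protocol gives no intake, harm or count for this age, so the correction is precautionary. The other is that feeding siblings damages the trial: the lower age limit for siblings has no bearing on the enrolled children's serum zinc endpoint, on the planned group sizes or on the equivalence conclusion.

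**What to change.** In the supply sentence, replace the reference to all under-fives with *the other children aged 6-59 months*, and leave the referral sentence that follows unchanged. An infant who turns 6 months during the study is then supplied from that point, and siblings aged 37-59 months stay covered.

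No new procedure is needed. Sibling age can be asked at the visits already planned in *Recruitment of study participants* ("Door-to-door visits will be done to identify families with the target children"). The sources are those already listed in *Anthropometric measurements* ("Age as per birth date (Child Health Cards) will be taken"), with the parent's estimate or a local event calendar where no card exists. The one drawback is that a few young infants in these households are not supplied until they reach 6 months.
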